##### Aim 2 assessment procedures

2.1.3.4

**Weekly assessments during the UP skills phase**. Participants will complete brief weekly assessments (approximately 15 min) prior to each UP session via REDCap. These assessments are intended to capture weekly changes in symptoms across the skills phase while minimizing immediate influence of session content on participant responses. Measures will assess depression, anxiety, posttraumatic stress symptoms, dissociation, affect, alcohol and other drug use, and alcohol craving. In addition to informing clinical monitoring, these measures will permit exploratory examination of symptom trajectories during treatment. Participants will receive remuneration of $10 for each weekly assessment completed before UP sessions, up to $40 across the UP phase.

**Daily assessments during the EW phase.** Participants will complete brief daily assessments (∼5–7 min)immediately following each writing session and prior to the telehealth clinician check-in. Daily measures will capture proximal, state-level responses to repeated engagement with emotionally salient material, including anxiety/arousal, emotional engagement, dissociation, substance use and craving, and exposure dose indicators (e.g., repeated writing about the same versus different event[s]). Administering assessments before the clinician check-in is intended to characterize immediate responses to the writing task itself, minimize recall bias, support safety monitoring, and permit exploratory examination of inhibitory learning– and emotion regulation–related processes during the writing phase. Elevated distress or dissociation will be reviewed during the same-day clinician check-in and addressed through grounding, safety monitoring, and reinforcement of relevant UP skills. Participants will receive remuneration of $10 for each daily assessment completed following each writing session ($50 total across the EW phase).

**Follow-up assessments.** Participants in the immediate treatment condition will complete follow-up assessments 1 week following intervention completion. Participants in the waitlist condition will complete an equivalent assessment following the 6-week wait period (i.e., prior-to-treatment assessment), as well as post-treatment and 1-week follow-up assessments after completing RISE. Follow-up assessments will include a 30-min online self-report survey and a virtual clinician-administered assessment (∼2 h) consisting of the 30-day TLFB, SCID-5 Substance Use Disorders module, and CAPS-5. Participants will have up to 2 weeks from the target assessment date to complete follow-up procedures and will receive reminder emails. Participants will receive $50 for completing follow-up assessment (either 1-week follow-up following intervention completion for those in the immediate treatment condition or the 1-week assessment following the wait period for those in the waitlist condition).

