##### Aim 2 procedures

2.1.3.3

Following eligibility confirmation through the electronic screening survey and synchronous virtual screening, Aim 2 participants will complete online self-report assessments and virtual clinician-administered assessments. Participants randomized to immediate treatment will complete assessments at baseline, post-treatment (following completion of RISE UP modules and EW sessions), and 1-week follow-up. Participants randomized to the 6-week waitlist condition will complete assessments at baseline, post-waitlist/prior to treatment initiation, post-treatment, and 1-week follow-up (see Fig. 1).

Clinician-administered assessments will include the 30-day Timeline Followback (TLFB) [129] to assess alcohol use quantity and frequency; the Structured Clinical Interview for *DSM-5* (SCID-5) Substance Use Disorders module [130] to characterize current and past alcohol/drug use disorders; and the Clinician-Administered PTSD Scale for *DSM-5* (CAPS-5) [131] to determine at least subthreshold PTSD diagnosis and symptom severity. During the baseline virtual visit, participants will schedule all planned intervention sessions and receive a scheduling handout, email reminders for appointments, and clinician contact information for rescheduling if needed. Participants will receive $50 total for completion of baseline self-report and clinician-administered assessments regardless of condition.

**Randomization.** After completion of the baseline self-report and clinician-administered assessments, Aim 2 participants will be randomized 1:1 (unstratified) using REDCap to either immediate treatment receipt or a 6-week waitlist control condition. Randomization assignments will be accessible only to the project coordinator responsible for scheduling participants into the appropriate study timeline. All other study personnel, including assessors, interventionists, and the Principal Investigator, will interact with participants using study IDs and will not be informed of whether participants were assigned to immediate treatment or waitlist. Interventionists and supervisors will know only when a participant is cleared to begin RISE, regardless of whether that occurs immediately after baseline or after the waitlist period. Clinician assessors conducting outcome evaluations will remain masked to condition assignment.

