**Immediate condition.** Participants randomized to the immediate condition will begin RISE within 2 weeks following randomization. Participants will be allowed up to 6 weeks to complete the intervention, including four UP-based sessions delivered across five weeks followed by five days of EW completed within 1 week. Participants will also complete post-treatment assessments and a 1-week follow-up assessment. Limited scheduling flexibility (e.g., brief rescheduling, temporary pauses) will be permitted and documented to accommodate participant burden, availability, or clinically indicated needs while maintaining intervention and assessment sequencing.

**Waitlist control condition.** Participants randomized to the waitlist condition will complete baseline assessments identical to those completed by the immediate treatment group and then enter a 6-week wait period. Following the wait period, participants will complete a post-waitlist assessment (i.e., prior-to-treatment assessment) identical to the immediate treatment group's post-treatment assessment. Participants in the waitlist condition will then begin RISE within approximately two weeks of the post-waitlist assessment and will follow the same intervention timeline and assessment schedule as the immediate treatment group, including post-treatment and 1-week follow-up assessments. Providing RISE following the wait period is intended to maintain access to care and support ethical study conduct.

**RISE intervention.** RISE is a brief, telehealth-delivered intervention consisting of four once-weekly adapted UP skill sessions (Modules 2–5) followed by five consecutive days of EW (see Fig. 1). UP sessions will focus on understanding emotions, cultivating mindful emotional awareness, enhancing cognitive flexibility, and countering emotion-driven behaviors in contexts relevant to SMW/TGD people's experiences, such as using alcohol to cope with anticipated stigma, trauma, or difficult emotional states, and relying on avoidance coping to manage distress. Clinicians will be clinical psychology doctoral students trained in the RISE protocol.

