##### Acceptability and feasibility

2.1.3.6

Acceptability and feasibility of RISE will be evaluated across both aims using participant and provider feedback, quantitative implementation indices, and qualitative data.

**Aim 1 pre-pilot adaptation.** SMW/TGD community members and providers will review draft intervention materials and provide feedback regarding clarity, cultural responsiveness, safety, burden, feasibility, and perceived fit with treatment targets and mechanisms. Feedback will be synthesized using an adaptation matrix to identify areas of convergence, divergence, and recommended revisions. This process will inform iterative refinement of intervention materials, procedures, and delivery prior to Aim 2 pilot testing.

**Aim 2 pilot testing.** Treatment feasibility will be operationalized using intervention uptake, completion, retention, implementation burden, and data completeness metrics. Intervention completion will be defined *a priori* as completion of ≥3 of 4 UP sessions and ≥3 EW sessions, consistent with existing recommendations [101,115]. Retention will be indexed by completion of post-treatment and follow-up assessments. Additional feasibility indicators will include recruitment yield, screening-to-enrollment ratios, assessment completion rates, prompt compliance, missing data, staff effort, and frequency of risk assessments or safety escalations.

Acceptability will be assessed at post-treatment and follow-up using standardized measures, including the Client Satisfaction Questionnaire–8 (CSQ-8), Working Alliance Inventory–Short Form (administered following the Unified Protocol phase), Reactions to Research Participation Questionnaire–Revised (RRPQ-R), and a single-item recommendation rating. Participants will also provide brief open-ended feedback regarding study participation.

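### The stated $50 follow-up payment falls on different visits in the two arms, so visits that should match carry different stated incentives and could be missed at different rates

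*Protocol article*

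**What the plan says.** All references are to the protocol article.

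- **Payment rule (2.1.3.4, follow-up assessments).** "Participants will receive $50 for completing follow-up assessment (either 1-week follow-up following intervention completion for those in the immediate treatment condition or the". On the other side of that either/or, the visit named is a "1-week assessment following the wait period for those in the waitlist condition". This is one payment, tied to one named visit per arm.
- **Counterpart of the post-waitlist visit, first account (2.1.3.3, waitlist control condition).** The assessment after the wait is "identical to the immediate treatment group's post-treatment assessment". Section 2.1.3.5 pairs the same two visits when it says when new outside treatment will be assessed.
- **Counterpart, second account (2.1.3.4).** Directly after describing the immediate arm's 1-week follow-up, the text says "Participants in the waitlist condition will complete an equivalent assessment following the 6-week wait period (i.e., prior-to-treatment assessment", and then "as well as post-treatment and 1-week follow-up assessments after completing RISE".
- **Visits in the immediate arm (2.1.3.3).** "Participants randomized to immediate treatment will complete assessments at baseline, post-treatment (following completion of RISE UP modules and EW sessions), and 1-week follow-up".
- **Retention (2.1.3.6).** "Retention will be indexed by completion of post-treatment and follow-up assessments".
- **Other payments.** $50 at baseline in both arms (2.1.3.3), up to $40 for weekly assessments and $50 for daily writing-phase assessments (2.1.3.4).
- **Fig. 1.** Its caption says that it details compensation. The figure itself is not available here.

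**The concern.** Retention and assessment parameters are among the main outputs of this pilot (2.1.4) and will inform the definitive trial. A follow-up assessment takes about two and a half hours (a 30-minute survey plus an interview of about 2 hours), so a $50 payment could plausibly affect whether people attend. If the two sides of the randomised comparison carry different incentives, or if the same visit after RISE is paid in one arm only, an attendance difference between arms may reflect the payment schedule as well as the intervention. Missing assessments at the comparison visit also feed the time-by-arm models in 2.1.5.2.

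**Working it through.** **Step 1. Reproduce the plan's own payment figures.** Weekly: 4 × $10 = $40. Daily: 5 × $10 = $50. Both agree with the text.

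**Step 2. Map each stated payment to its visit.**

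| Visit | Immediate arm | Waitlist arm |
|---|---|---|
| Baseline | $50 | $50 |
| Post-waitlist | no such visit | $50 |
| Weekly assessments, skills phase | up to $40 | up to $40 |
| Daily assessments, writing phase | up to $50 | up to $50 |
| Post-treatment | none stated | none stated |
| 1-week follow-up after RISE | $50 | none stated |
| **Total stated** | **$190** | **$190** |

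The totals agree (50 + 40 + 50 + 50 = 190). Only the placement of the last $50 differs.

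**Step 3. Compare the two accounts of the randomised contrast.**

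- Post-treatment against post-waitlist (2.1.3.3 and 2.1.3.5): no stated payment against $50.
- 1-week follow-up against post-waitlist (2.1.3.4): $50 against $50.

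Section 1.7 places the clinical outcomes at post-treatment, which favours the first account. The wording in 2.1.3.4 that places a 1-week assessment after the wait period occurs nowhere else. Sections 2.1.1 and 2.1.3.3 describe a post-waitlist assessment with no one-week lag.

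**Step 4. Compare the visits after RISE.** This does not depend on Step 3. Post-treatment has no stated payment in either arm. The 1-week follow-up has $50 in the immediate arm and none stated in the waitlist arm. Of the two visits that define retention in 2.1.3.6, the text states payment for one in the immediate arm and for neither in the waitlist arm.

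**Step 5. Would a payment-driven gap be noticed?** Inputs from 2.1.4: 30 per arm and about 20% attrition, so 30 × 0.80 = 24 retained per arm (Wilson 95% interval 63% to 90%). The documents give no attendance rates by payment, so the gaps below are assumed and centred on 80%. The 95% half-width of the difference is 1.96 × √[p₁(1−p₁)/30 + p₂(1−p₂)/30]. At 80% in both arms this is 1.96 × √(2 × 0.16/30) = 0.20.

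| Assumed gap | 95% half-width | Chance of detecting it |
|---|---|---|
| 5 points | 20 points | 7% |
| 10 points | 20 points | 16% |
| 15 points | 20 points | 30% |
| 20 points | 20 points | 49% |

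A gap of any of these sizes could easily pass unnoticed. Nothing in the documents shows that one will occur.

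**Step 6. Possible effect on the clinical contrast, by assumption only.** If non-attenders differ from attenders by d SD in both arms, the difference in observed means shifts by (gap in missing fraction) × d. For gaps of 0.05 to 0.20 and d of 0.3 to 0.8, this runs from 0.05 × 0.3 = 0.015 to 0.20 × 0.8 = 0.16 SD. With 24 per arm, the standard error of a standardised difference is about √(2/24) = 0.29.

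**The case against.** A reader might infer that the RISE side of the comparison and the waitlist arm's visits after RISE are unpaid, and that retention and outcomes are therefore distorted by arm. The documents do not support that.

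- **Silence is not a statement of no payment.** The text names two paid follow-up visits and says nothing about the others. Fig. 1 may pay them. This stands, and it is why the point is worded as payment not stated. It does not remove the problem: if Fig. 1 pays more visits, the either/or sentence in 2.1.3.4 is wrong as it reads, and if Fig. 1 agrees with that sentence, the asymmetry is real.
- **The pairing is ambiguous.** On the account in 2.1.3.4, the paired visits carry $50 each. This also stands, but the two sections then disagree about which visit is the comparison, and the 1-week follow-up after RISE still differs between arms.
- **Other payments blur the net incentive.** Before its post-treatment visit the immediate arm can earn $40 + $50 = $90, while the waitlist arm has no stated payment between baseline and its post-waitlist visit. The direction of any effect on attendance therefore cannot be derived.
- **Retention is not defined on the post-waitlist visit.** Section 2.1.3.6 names post-treatment and follow-up only. A gap at the comparison visit would bear on outcome missingness more directly than on the retention index.
- **The clinical effect is likely to be small against the noise.** The assumed shifts in Step 6 are at most about half of one standard error. They apply to differences in observed means, and the planned mixed models may absorb part of them. The protocol already calls its clinical estimates preliminary.

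**Conclusion.** The point holds as an inconsistency in the payment and visit schedule that is easily avoided. The text places one $50 on the immediate arm's 1-week follow-up and on the waitlist arm's post-wait visit, and the protocol gives two accounts of which immediate-arm visit is the counterpart of the latter. On the account in 2.1.3.3, the two sides of the randomised contrast carry different stated incentives. On either account, the 1-week follow-up after RISE does.

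The consequence is a plausible risk of arm-specific missingness in retention and in the preliminary contrast. Its size and direction are unknown, and the figures in Steps 5 and 6 rest on assumed gaps. The conclusion is conditional on Fig. 1.

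**What to change.** 1. Settle, consistently across 2.1.3.3, 2.1.3.4 and Fig. 1, which immediate-arm visit is the counterpart of the post-waitlist visit, and correct or explain the one-week label attached to the wait period.
2. Replace the either/or payment sentence with the payment at each visit by arm, giving the same amount for the same visit in both arms: at the randomised comparison (post-treatment against post-waitlist) and at each visit after RISE.

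**Cost.** A payment amendment, best made before Aim 2 recruitment (anticipated August 2026). Paying $50 at every visit adds at most 30 × $50 (immediate arm, post-treatment) + 30 × 2 × $50 (waitlist arm, two visits after RISE) = $1,500 + $3,000 = $4,500. It adds less if Fig. 1 already pays some of these visits.

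**Cheaper option.** Moving the immediate arm's $50 to post-treatment adds nothing and equalises the post-treatment against post-waitlist comparison. It leaves the 1-week follow-up after RISE without a stated payment in both arms, although that visit counts towards retention. It also leaves the post-treatment visit after RISE paid in the immediate arm only, unless the waitlist arm is paid there too, at 30 × $50 = $1,500.

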##### Adherence, fidelity, and contamination procedures

2.1.3.5

In the immediate arm, adherence will be indexed by UP session attendance (0–4). EW adherence will be indexed by writing completion (0–5), system-captured time-on-task with a minimum writing of ≥15 min, and word count. EW engagement will be characterized using brief post-writing indicators collected immediately following each session, including self-reported prompt adherence, emotional engagement, avoidance, and perceived disclosure.

Prior to data collection, clinician assessors will complete standardized training in study procedures, clinical risk assessment, and administration of clinician-rated measures, including practice administration and reliability calibration. Standardized fidelity and competency checklists will be used to monitor assessment and intervention delivery, with approximately 20% of recorded sessions reviewed by the Principal Investigator and clinical supervisor. Ongoing weekly supervision will support fidelity, reliability, and procedural adherence. Prior to participant contact, interventionists will complete standardized training in the RISE protocol, including UP principles, EW procedures, telehealth delivery, SMW/TGD-affirming care, clinical risk assessment, and study procedures through manual review, didactics, and role-plays.

Participants may discontinue participation at any time without penalty or request scheduling or pacing modifications due to burden, emotional distress, or competing responsibilities. Clinicians will monitor distress, dissociation, alcohol-related risk, suicidality, and other safety concerns during treatment sessions and EW check-ins. When clinically indicated, sessions may be paused, rescheduled, or shifted toward grounding, coping review, safety planning, crisis intervention, or referral to higher levels of care. Initiation of new trauma-focused or alcohol treatment during the study period will be assessed in the post-treatment or post-waitlist assessments. Concomitant treatment will be considered in sensitivity analyses.

Trial safety procedures will include monitoring for serious adverse events, acute suicidality, mania, psychosis, or other exclusionary clinical concerns identified during treatment or clinician-administered assessments. If exclusionary thresholds are met, participation may be discontinued and referrals initiated. The trial may be paused or terminated if continuation is deemed unsafe by the Principal Investigator and/or Institutional Review Board (IRB) based on emerging safety concerns, adverse events, or other clinically significant risk indicators.

##### Acceptability and feasibility

2.1.3.6

Acceptability and feasibility of RISE will be evaluated across both aims using participant and provider feedback, quantitative implementation indices, and qualitative data.

**Aim 1 pre-pilot adaptation.** SMW/TGD community members and providers will review draft intervention materials and provide feedback regarding clarity, cultural responsiveness, safety, burden, feasibility, and perceived fit with treatment targets and mechanisms. Feedback will be synthesized using an adaptation matrix to identify areas of convergence, divergence, and recommended revisions. This process will inform iterative refinement of intervention materials, procedures, and delivery prior to Aim 2 pilot testing.

**Aim 2 pilot testing.** Treatment feasibility will be operationalized using intervention uptake, completion, retention, implementation burden, and data completeness metrics. Intervention completion will be defined *a priori* as completion of ≥3 of 4 UP sessions and ≥3 EW sessions, consistent with existing recommendations [101,115]. Retention will be indexed by completion of post-treatment and follow-up assessments. Additional feasibility indicators will include recruitment yield, screening-to-enrollment ratios, assessment completion rates, prompt compliance, missing data, staff effort, and frequency of risk assessments or safety escalations.

Acceptability will be assessed at post-treatment and follow-up using standardized measures, including the Client Satisfaction Questionnaire–8 (CSQ-8), Working Alliance Inventory–Short Form (administered following the Unified Protocol phase), Reactions to Research Participation Questionnaire–Revised (RRPQ-R), and a single-item recommendation rating. Participants will also provide brief open-ended feedback regarding study participation.

To deepen understanding of intervention fit, burden, and implementation barriers/facilitators, semi-structured qualitative exit interviews will be conducted with 20 participants selected across study conditions and treatment completion patterns. Immediate-treatment participants will be interviewed following completion of post-treatment procedures, and waitlist participants will be interviewed following crossover completion of RISE. Participants who discontinue or do not initiate or complete treatment will remain eligible for interviews, when feasible, to inform understanding of barriers to engagement and intervention refinements. Interviews and focus groups will be audio-recorded and transcribed verbatim. Transcripts will be deidentified and analyzed using rapid, framework-guided thematic methods to generate refinements [134].

##### Data management and quality assurance

2.1.3.7

Self-report, EW, and study process measures will be administered via REDCap and stored on secure, university-approved servers using predefined validation procedures (e.g., range checks, required fields, missing-data flags). EW completion and time-on-task metrics will be automatically captured, and selected writing characteristics (e.g., prompt adherence, engagement indicators) will be coded for analytic purposes.

Data quality procedures will include automated screening for fraudulent or bot-like responding (e.g., attention checks, response-pattern review), routine audits of data completeness and consistency, and double-coding of qualitative transcripts. Detailed data management, coding, and quality assurance procedures will be maintained in a separate Data Management Manual.

Participant information will be stored in password-protected, encrypted systems and accessible only to authorized study personnel responsible for recruitment, scheduling, follow-up, and safety monitoring. Audio recordings will be stored separately from identifying information, and deidentified datasets will be generated for analysis. Data will be retained and destroyed according to IRB-approved procedures. Given the minimal-risk nature of the protocol, brief intervention duration, and clinical monitoring, a Data Monitoring Committee is not planned.

